### (a) Background of research

#### The importance of timely care-seeking in the context of AMI

Acute myocardial infarction (AMI) is the acute and severe manifestation of coronary artery disease (CAD), resulting from a sudden cessation of coronary blood flow due to thrombotic occlusion. It is an emergency requiring immediate medical attention. The amount of myocardial necrosis from the moment of occlusion is curvilinear with a greater extent of cell death occurring in the early hours. In addition, the efficacies of reperfusion therapies are also highly time-dependent. Despite the types of reperfusion strategies, their efficacies diminish over time with a striking benefit observed within the first 2 hours of symptom onset. For instance, using an analysis of 22 trials, the researchers documented a substantial reduction in mortality when the thrombolytic drugs were administered within 2 hours of symptom onset. Likewise, De Luca et al. reported that the risk of 1-year mortality was raised by 7.5% for every 30-minute delay in receiving the percutaneous coronary intervention. Other than the ischaemic effect, AMI patients are prone to develop fatal arrhythmias in the early hours of disease onset. According to the latest statistics, majority of AMI-related deaths occur in the first hour of symptom onset are related to ischaemia-induced ventricular arrhythmias, which accounts for up to 70% of the CAD-related deaths. For this reason, early access to emergency medical care for prompt defibrillation and cardiopulmonary resuscitation is of paramount importance for AMI patients. Moreover, using ambulance for transporting to hospitals enables patients to get immediate emergency care from paramedic if fatal arrhythmia occurs. In Hong Kong, up to 50% of the patients did not use ambulance during an AMI attack, which greatly jeopardize their chance of survival. Indeed, AMI survivors are prone to have recurrent events and high mortality risk. A representative trial reported that up to 54% of patients presented with new myocardial ischaemia within the first year of AMI, while another large population trial showed a 17.4% of 1-year risk of re-infarction. Given that the time taken by patients to make their care-seeking decisions accounts for the major portion of the total ischaemic time and the high recurrent rates among the AMI survivors, there is a pressing need to develop effective interventions to promote timely care-seeking in AMI patients.

#### Nature of AMI care-seeking behaviour

Care-seeking is a product of how people perceive, evaluate and respond to symptoms. This behavioural process not only relies on people's knowledge about the disease, but also their beliefs and attitudes regarding care-seeking. Beliefs reflect people's opinions about the truth of a proposition, while attitudes are mental positions regarding something known. Both beliefs and attitudes reflect people's behavioural intention, which is the best predictor of a behaviour. According to the major

theories in explaining illness behaviours, patients often make care-seeking decisions within a complex framework, where multiple factors interplay to influence their care-seeking decision. Indeed, the symptom manifestations of AMI vary considerably from time to time, as well as among different individuals. A substantial proportion of patients present with atypical symptoms, which create challenges for the patients during symptom evaluation. This complexity contributes to the extensively documented AMI care-seeking delay, even in patients with a prior AMI experience. Moreover, the nature of the care-seeking behaviour differs from other health-related behaviours in terms of the duration of learning history and behavioural rehearsal. For other behaviours, patients have a long learning history and plenty of opportunities for behavioural rehearsal. Contrarily, care-seeking in the context of AMI involves a behaviour with little or no opportunity for learning and rehearsal, which poses another challenge to patients. In such an endeavour with an absence of actual experience, providing a virtual but vicarious experience is essential for promoting timely care-seeking in AMI patients.

#### The complex phenomenon of AMI care-seeking behaviour

Extensive research has been published to report the factors associated with care-seeking delays in AMI patients. These factors include sociodemographic (e.g., age, gender), clinical (e.g., types of AMI, history of diabetes), cognitive (e.g., symptom attribution), emotional (e.g., fear, denial) and contextual (e.g., symptom onset time and place) factors. However, most of these studies focused on examining the direct effects of various factors on patients' prehospital delay. These studies offered important information to inform the high risk group of having a prolonged care-seeking delay, yet the underlying mechanism remains largely unknown. To address this gap in the literature, the principal investigator (PI) developed and validated an integrative model to explain the phenomenon of care-seeking delay in AMI patients. This integrative model was developed on the basis of the most up-to-date empirical evidence and several behavioural theories, including Leventhal's Self-Regulatory Model of Illness Behaviour, the Health Belief Model and Dracup's integrated model. A common postulation of these theories is that upon the onset of some somatic sensations, a cognitive process is evoked to give meaning to the stimuli, which in turn shapes one's illness behaviour. According to these theories, people's care-seeking decisions can be seen as driven by two perceptual-cognitive processes, an initial 'illness labelling' process and a subsequent 'illness interpretation' process. At the onset of symptoms, the initial perceptual-cognitive process is initiated, where people cognitively interpret their symptoms to make a lay diagnosis. This diagnosis triggers the subsequent process of illness interpretation. Patients' interpretation and perceptions of the diagnostic label determine their tendency to seek medical care. This integrated theoretical model was tested by the PI in a group of 301 AMI patients. The findings confirmed the two perceptual-cognitive processes in determining patients' care-seeking behaviours. According to the final model, timely care-seeking behaviours in the context of AMI depend on whether patients can correctly attribute their symptoms to AMI. This cognitive process in labelling the symptoms relies on a good understanding of the disease nature, awareness of one's susceptibility to AMI and higher alertness to atypical AMI manifestations. After this initial

labelling process, the following process in interpreting the illness in terms of perceiving severe consequences and the associated negative emotional arousal further prompt patients to seek care. In addition to these two perceptual-cognitive processes, several contextual factors also influence care-seeking behaviours. These factors include patients' perceived barriers to care-seeking and the presence of positive cues to care seeking from the significant others. An effective intervention to promote timely AMI care-seeking behaviours, hence, needs to guide the patients through these perceptual-cognitive processes, assist them to identify any of the barriers and misbeliefs hindering their care-seeking behaviours throughout the process, then provide resolving methods and clarify any misunderstandings accordingly. As AMI is life-threatening and unpredictable, preparing patients to have timely care-seeking must take place before they are exposed to the situation. In such case, creating a virtual but vivid experience for an AMI attack episode is crucial to provide a platform to precisely guide the patients to rehearse every decision making in the two perceptual cognitive processes. Interactive and individualized approaches are needed to address the influence of contextual factors on actual care-seeking behaviours.

#### Narrative approach in health behaviours and its theoretical underpinning

A narrative form of communication is emerging as a powerful and promising alternative educational method to optimise health promotion and education. A narrative is defined as a "coherent story with an identifiable beginning, middle, and end that provides information about scene, characters, and conflict; raises unanswered questions or unresolved conflict; and provides resolutions." Education through the narrative approach can offer a vicarious learning opportunity by creating a vivid experience for patients. A narrative approach can be achieved through a wide range of modalities, such as entertainment education using cartoon or drama, testimonials and storytelling. Such an approach has the unique ability to mentally engage the audiences by transporting them into a narrative world, which leads them to engage with the events in the story. As compared to the conventional educative approach to change health behaviours, a narrative approach is more favourable in facilitating attention, enhancing interpretation of a complex situation (e.g., AMI attack), rehearsing complex decision making, recognising possibly emotional responses, modelling desirable behaviours and offering support. In addition, narrative communication is effective in breaking down cognitive resistance to behaviour-change messages. The theoretical underpinning of the narrative approach is grounded in the observational learning of Social Cognitive Theory (SCT). The underlying rationale for observational learning was initially proposed by Sheffield in 1961, where observation of a model in performing a certain action was proposed to provide the learner with a cognitive blueprint of the action or a standard of reference for how to perform the action, which served as a crucial guide for the learner to reproduce it later. This initial idea was extended by Bandura in SCT. This theory posits that modelling-based interventions play a role in influencing the outcomes through their impact on one or more of the four observational learning processes. They include: 1) the attention process which governs the sensory registration of the modelled behaviour; 2) the retention process where the modelled behaviour is symbolically coded as cognitive representations in the memory for regulating

future behaviour; 3) the production process where the component actions are integrated into patterns that require the enacting of the behaviour; and 4) motivation process where the acquired skills will be converted to overt behavioural performance. The narrative approach for behavioural modelling addresses all these four processes in promoting health-related behaviours.

#### Empirical effects of narrative approach to promote health-related behaviours

Emerging evidence suggests that the narrative approach has become a powerful tool for health promotion in vulnerable populations. For instance, Houston et al. examined the effects of a narrative-based intervention delivered through an interactive DVD to promote blood pressure control. The intervention included narrative stories collected from the patient population, which solicited personal experiences about hypertension control. The storytellers described how they lived with hypertension, how to interact with physicians and offered strategies to increase medication adherence. Patients with baseline uncontrolled blood pressure showed significant reduction in both systolic (11.21 mmHg) and diastolic (6.43 mmHg) blood pressures as compared to the attention placebo group. Such an extent of improvement indicates that the narrative-based intervention through storytelling produced changes in blood pressure was far more effective than the other non-pharmacological behavioural interventions, with its effect even comparable to that of pharmacological interventions. Similarly, the narrative approach has been adopted to promote different types of health-behaviours. A recent meta-analysis reported that narrative interventions were significant in promoting health behaviours in disease detection (e.g., mammogram test) as well as disease prevention (e.g., cancer prevention, human papillomavirus vaccination). Cole examined the effects of a series of interactive written narratives to simulate real-life situations when teaching problem-solving and decision-making skills in handling emergency situation in farm workers and coal miners. The participants had to make a decision and respond at designated critical junctures. They were allowed to proceed if they made a safe option. Otherwise, they were directed to give further consideration to available alternatives and make another decision. This narrative intervention significantly improved the decision-making skills among the workers. Such a narrative approach with real-life scenarios is particularly useful for training people's problem solving and decision making in situations of rare occurrence, where the chance for behavioural rehearsal is slim. The narrative approach offers an important cognitive rehearsal for their decision-making as well as the actions that they may need to implement later in their real-life situations.

The major gap in the current literature is that even though substantial evidence indicated the positive and significant effects of narrative interventions on promoting various health behaviours, no study has applied the narrative approach to promote proper care-seeking behaviours among AMI patients. Nevertheless, these previous studies offered important insight into how to develop and use a narrative approach in health promotion and educative interventions. However, these studies failed to describe the strategies to actively engage participants in the learning process. Moreover, strategies to enhance knowledge and skill retention were not adopted in their interventions, which might limit more persistent beneficial effects. Taking measures to enhance knowledge and skill retention is of particular importance when promoting prompt care-seeking behaviours in the context of AMI, as future attacks

may occur after an extended period of time.

#### Enhancing timely care-seeking by a narrative approach through behavioural modelling

Based on the above literature review, a narrative approach for behavioural modelling appears to have high potential to engage high risk patients to have AMI attacks in the two perceptual-cognitive processes in a guided virtual environment. In order to enhance the retention of acquired knowledge and skills, an interactive multi-media method should be integrated. In particular, an interactive video presentation may be a more effective means to create virtual but vivid experience of an AMI attack to the patients. Interactive stimulating questions can be inserted throughout the video to guide multiple decision-making actions throughout the two perceptual-cognitive processes. This can allow a mental rehearsal and self-reflection, which is effective in shaping patients' future care-seeking behaviours. To further strengthen and transfer behavioural modelling, extreme case model (i.e., patients who demonstrated prompt care-seeking and delay care-seeking in real life) can be invited to share their illness experience. This modelling-based approach provides a vicarious learning environment that resembles actual experience. The investigation team thus hypothesises that a modelling-based narrative approach through storytelling using an interactive video presentation, interactive discussion, and extreme cases role modelling would be an effective approach to address the perplexing and persistently prolonged care-seeking delay in AMI patients.

#### Work done by us

This study proposes to address the findings of research conducted by the PI, which tested an integrative theoretical model explaining the care-seeking delay in AMI patients. This integrative model serves as important groundwork to guide the development of an intervention to address the issue of prolonged care-seeking delays among AMI patients. In addition, the investigation team has developed and validated a risk scoring system to estimate the risk of people developing atypical AMI symptoms. Our previous work indicates that people of female gender, older age, with diabetes mellitus, a prior history of AMI and without hyperlipidaemia are more prone to present with atypical symptoms during an AMI attack. This simple scoring system will be incorporated into this study to guide the provision of tailor-made information to patients. The team of investigators, with a strong track record in cardiac care, narrative-based intervention for caregiver empowerment, patient empowerment model for self-care enhancement, and psychosocial interventions, have developed the protocol for the modelling-based narrative intervention to increase the behavioural intention for prompt care-seeking among patients at risk of developing AMI.

#### **(b) Research plan and methodology**

The aim of the study is two-fold: i) to evaluate the effects of a modelling-based narrative intervention on care-seeking beliefs, attitudes and knowledge, use of ambulance and prehospital care-seeking delays among AIM patients, and ii) to explore how and why the intervention affects the care-seeking behaviours from the patients' perspective. The behavioural intention, as reflected by the care-seeking beliefs and attitudes, are the primary outcomes, while AMI knowledge, use of ambulance and prehospital delays in care-seeking in AMI attacks are the secondary outcomes. The research hypothesis

of the first aim is that AMI patients who receive the modelling-based narrative intervention will report better changes in: i) care-seeking beliefs, ii) care-seeking attitudes, iii) AMI-related knowledge, iv) more likely to use ambulance, and v) shorter prehospital delays when AMI symptoms occur at 3, 12, and 24 months after the intervention, than those who receive didactic education on AMI care-seeking.

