### Study design

This is a sequential mixed-method study consisting of a randomised double-blind controlled trial and an exploratory qualitative study. The study implementation protocol is outlined in Figure 1. A research assistant (RA1) will recruit eligible participants from the cardiac clinics and wards of four regional hospitals in Hong Kong. The study sites are leading hospitals providing cardiac care services within the region. He/she will collect participants' baseline (T0) demographic data and study variables during a face-to-face interview. Block randomisation with a block size of 8, 10 or 12 will be used to ensure even distribution of participants between the two study groups. The block size and the respective allocation sequence to the intervention group receiving a modelling-based narrative intervention (by RA1) and control group receiving a didactic education (by RA2), will be determined by a computer-generated sequence. Participants chronologically recruited to the study will be allocated to the study groups by RA1 according to the computer generated sequence. Another independent RA (RA3), who is blinded to the study group allocation, will collect the post-intervention data. To detect short-term and long-term intervention effects, the outcome variables will be measured repeatedly at 3 (T1), 12 (T2) and 24 (T3) months following baseline data collection for both study groups. This extended period of outcome evaluation permits the study to detect the intervention effects on participants' actual care-seeking behaviours. Previous studies indicated that approximately 16% of these patients experienced AMI symptoms within two years. In the data collection telephone calls, the RA3 will enquire about whether the participants have been admitted to an emergency department with the experience of AMI symptoms. The study participants and their next of kin are strongly advised to contact the RA if they have been admitted due to a possible AMI attack.

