### Study participants

Patients will be eligible to join the study if they are (1)  $\geq 18$  years of age, (2) living in the community, (3) with a confirmed diagnosis of a prior AMI attack, (4) consent to participate and (5) those who can read Chinese. Individuals who do not understand Cantonese, with impaired communication ability, psychiatric problems or impaired cognitive functioning (i.e. Abbreviated Mental Test  $\leq 6$ ) which may hinder participation in the interventional activities will be excluded. For the RCT study, the sample size is determined on the basis of a large-scale RCT examining the effect of a brief nursing educational intervention on care-seeking knowledge, attitudes and beliefs related to AMI in people with CAD. The effect sizes for knowledge, attitudes and beliefs were 0.39, 0.24 and 0.23 at 3 months after the intervention. In consideration of both clinical relevance and previous study findings, the sample size of this study is determined to give the study adequate power to detect at least a small to medium effect size on the primary outcomes. Using PASS 13 (NCSS, Kaysville, USA), it is estimated that a sample size of 252 subjects per study arm would give the study 80% power at 5%

level of significance to detect an effect size as small as 0.23 on our primary outcomes between the control and intervention arms at the post intervention time points. Further allowing for a potential dropout rate of up to 20%, a total of 315 subjects per arm will be recruited. For the qualitative phase, a criterion sampling of 30 participants who have received the modelling-based narrative intervention will be invited to join on the basis of their prehospital delay time, which will be categorised into three groups:  $\leq 2$  hours,  $> 2$  and  $\leq 6$  hours, and  $> 6$  hours. The criterion is set according to the international AMI management guidelines, where such cut-offs are used to categorise patients into early, intermediate and late responders. A total of 30 participants will be recruited, with 10 participants for each category. Maximum variations in the sociodemographic and clinical profile of the participants will also be adopted in the sampling procedure to illustrate a wider range of data.

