#### Data analysis

For the RCT study, data analysis will be performed on an intention-to-treat basis. Baseline characteristics between the two study arms will be compared by t-test, chi-square or Fisher's exact test

where appropriate. A generalized estimating equation (GEE) model will be used to compare the differential changes on the outcomes across the time points T0, T1, T2 and T3 between the two study arms with adjustment for potential confounding variables. Baseline characteristics with p values < 0.25 for between-group difference will be considered as potential confounding variables. GEE model can account for intra-correlated repeated measures data and accommodate missing data caused by incomplete visits or dropout, provided that the data are missed at random, and thus are particularly suitable for intention-to-treat analysis without the need of imputation for missing data. All statistical analyses will be performed using IBM SPSS 23.0. All statistical tests will be two-sided and a p-value < 0.05 will be considered statistically significant. For the qualitative study, the audio-taped data will be transcribed verbatim. The investigation team will ensure accuracy of the transcription by cross-checking. Content analysis will be adopted to code the qualitative data on participants' perceptions and acceptability of the modelling-based narrative intervention. The analysis will also seek to understand why and how the study intervention influences patients' care-seeking behaviours. The codes units will be organised into categories and subcategories, which will be analysed for emerging themes. The trustworthiness of the qualitative analysis will be enhanced by audio-taping of the interviews, conducting an audit trail, involving two team members to code the qualitative data independently.

**Figure 1.** Study implementation protocol

[figure not shown]

**Figure 2.** Graphical presentation of the modelling-based narrative intervention protocol

[figure not shown]

**Table 1.** The storyline of the narrative video-based virtual heart attack experiencing session

**Background information of the model patient:** **[name]**, 58 year-old man, bus driver, non-smoker, with hypertension and hyperlipidaemia. He sustained a musculoskeletal injury over his chest region a week ago

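### Two primary outcomes, three hypothesised visits and a flat 5% level, with no primary time point, contrast or success rule, leave the error rate of the primary claim undefined and probably inflated

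*Protocol*

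**What the plan says.** Four parts of the Protocol bear on this point.

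- **Aims, under (b) Research plan and methodology:** "The behavioural intention, as reflected by the care-seeking beliefs and attitudes, are the primary outcomes". The hypothesis lists beliefs and attitudes as separate items and places the expected benefit "at 3, 12, and 24 months after the intervention". Outcome measures describes them as separate subscales (7 and 5 items). No composite of the two is defined.
- **Study design:** "the outcome variables will be measured repeatedly at 3 (T1), 12 (T2) and 24 (T3) months following baseline data collection". No visit is marked as the deciding one.
- **Study participants (sample size):** 252 per arm for 80% power at an undivided 5% level, to detect an "effect size as small as 0.23 on our primary outcomes between the control and intervention arms at the post intervention time points". The time points are plural. The only visit tied to a figure belongs to the source study: "The effect sizes for knowledge, attitudes and beliefs were 0.39, 0.24 and 0.23 at 3 months after the intervention".
- **Data analysis:** a GEE model is to "compare the differential changes on the outcomes across the time points T0, T1, T2 and T3 between the two study arms". The decision threshold is: "All statistical tests will be two-sided and a p-value < 0.05 will be considered statistically significant".

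The Protocol names no primary time point or contrast, gives no rule for how many primary outcomes must succeed, and makes no adjustment for multiple tests.

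**The concern.** With two outcomes and three follow-up visits there are six natural between-arm contrasts, and the stated threshold applies to each at full level. Because no passage says which result decides the trial, an analyst following the text could report a primary success from one subscale at one visit. A result seen only at 3 months means something different from one seen at 24 months, and the Protocol says it wants both short-term and long-term effects. If the deciding result is settled only after the data are seen, 5% no longer describes the chance of a false positive primary claim.

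**Working it through.** **Inputs from the Protocol.** Two primary outcomes; three follow-up visits (T1, T2, T3); two-sided 0.05 for each test; effect size 0.23; 252 per arm; 80% power.

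**Inputs assumed.** The Protocol gives no correlations. I use 0.3 to 0.8 between visits and 0 to 0.7 between the two subscales. Change-from-baseline contrasts share the same baseline; with an exchangeable correlation they correlate 0.5 across visits, which lies inside that range.

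**The plan's own figure.** The Protocol gives no family-wise error, so only its sample size can be checked (normal approximation, SD = 1):

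- n per arm = 2 × (1.960 + 0.842)² / 0.23² ≈ 296.7, so 297, not 252.
- At 252 per arm the expected z is 0.23 × √(252/2) = 2.582, so power = Φ(2.582 − 1.960) ≈ 73%.
- 252 is the answer for an effect size of 0.25: 2 × (1.960 + 0.842)² / 0.25² ≈ 251.2, so 252.
- The dropout step reproduces: 252 / 0.8 = 315.

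The shortfall at 0.23 is a separate matter. It is shown here because it sets the right baseline for the cost of the fix.

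**Reading A: any one of six contrasts counts as success.**

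- Independent tests: 1 − 0.95⁶ = 26.5%.
- Correlated tests, by simulation of six two-sided z statistics under the null (1,000,000 draws per cell):

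| Correlation between visits | Between subscales 0 | Between subscales 0.7 |
|---|---|---|
| 0.3 | 25% | 22% |
| 0.5 | 23.5% | 20% |
| 0.8 | 19% | 16% |

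**Reading B: one test per outcome, either may succeed.** This covers one overall group-by-time test per outcome, or one fixed visit.

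- Independent: 1 − 0.95² = 9.75%.
- Subscale correlation 0.7: 8.5% for the overall 3-degree-of-freedom tests, 8.3% for a single visit.

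**Reading C: both outcomes must succeed at one fixed visit.** The chance that both are falsely significant cannot exceed 5%, so there is no inflation and an undivided 5% is correct.

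**Effect of splitting the level on power.** At 0.025 the critical value is 2.241, so power at 0.23 with 252 per arm = Φ(2.582 − 2.241) ≈ 63%, against 73% at 0.05.

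**The case against.** Three counter-arguments deserve weight.

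*The GEE may be meant as one overall test per outcome.* The Data analysis wording allows that, and the figure is then about 8% to 10%. This stands. A reader might infer from the six contrasts that the trial's error rate simply is 20% to 25%. The Protocol does not support that as a general statement, because it needs six separate tests, success on any one of them, and correlations the document does not supply.

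*The hypothesis joins its items with an and, so both outcomes may have to succeed.* If both had to succeed at one fixed visit, nothing would be inflated. But the Protocol neither says that both must succeed nor fixes a visit, so this reading has to be supplied by the reader.

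*Multiplicity procedures and exact contrasts commonly sit in a SAP, and the 0.05 sentence is a general convention.* It is fair that the choice of procedure could sit there, and its absence alone would be no finding. But the Protocol is not merely silent. It sets two primary outcomes, three hypothesised visits, an undivided 5% in the sample size and a flat threshold for all tests. A SAP that split the level would depart from that text and from the basis of the sample size.

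It is also tempting to propose 12 months as primary, on the ground that time since last contact is most nearly equal between arms there. The schedule does not support this. Visits run from baseline in both arms, so the gap in time since last contact is the same at every visit, and relatively smallest at 24 months.

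**Conclusion.** The point holds in conditional form. The Protocol leaves open which result decides the trial while allowing every test the full 5%. The resulting family-wise error depends on the rule later adopted: 26.5% (independent) or about 16% to 25% (assumed correlations) if any of six contrasts suffices, about 8% to 10% with one test per outcome, and no more than 5% only under a both-must-succeed rule that the text does not contain. The structural finding rests on the Protocol's wording alone. The correlated figures rest on the assumed correlations stated above. The sponsor should correct this before analysis: it affects the primary claim and is cheap to settle.

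**What to change.** Before unblinding, amend the Protocol as follows.

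1. Name one primary contrast per outcome: either the between-arm difference in change at a single visit, chosen and justified by the sponsor, or one overall group-by-time test. The only effect sizes cited in the sample size section are at 3 months, so a later primary visit needs its own support. Identify the visit by its label (T1, T2 or T3), since the hypothesis counts months from the intervention and Study design counts from baseline.
2. Test beliefs and attitudes with the Hochberg procedure at two-sided 0.05 overall: claim both if both p-values are below 0.05; otherwise the smaller must be below 0.025. As a check, simulating this rule under the null with subscale correlations of 0 to 0.7 gave about 4.6% to 5.0%.
3. Label the other visits and the secondary outcomes as supportive, reported with confidence intervals.

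The cost is a few lines of text plus the sponsor's justification of the visit. If both outcomes reach 0.05, nothing is lost. If only one shows an effect, power at 0.23 with 252 per arm falls from about 73% to about 63%. That comparison starts from 73%; the gap to the stated 80% is the separate sample-size issue. Restoring 80% for a single outcome at 0.025 would need 2 × (2.241 + 0.842)² / 0.23² ≈ 359.4, so 360 per arm, or 360 / 0.8 = 450 with dropout. The level and the sample size are therefore best settled together.
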